### Theory of mind and language

Language ability has been consistently found to be associated with ToM performance [11, 26–30]. In particular, children’s understanding of mental state vocabulary, such as *think, believe, want, know*, and sentential complements such as “John believes/says it is raining” are linked to their ToM scores [29, 31–33]. There have been two main explanations for this relationship between ToM and language ability [11]. From the perspective of linguistic determinism, researchers argue that language plays a causal role in the development of ToM ability. In other words, children who lack language ability do not achieve ToM [31, 34]. However, there is much controversy over language's specific role in ToM development [26]. The domain-general perspective argues that the majority of the ToM tasks are verbal tasks and thus language is heavily needed in mental state understanding [35, 36].

A number of social-environmental factors have been found to be associated with children’s ToM development, including family size and the number of siblings [37–39], socioeconomic status [2], child’s sociolinguistic awareness [40], mother’s mind-mindedness [41], and mother–child mental state talk [6, 8]. These factors create a social-linguistically enriched environment for children to explore others’ mental stances and perspectives, and as such, children can respond appropriately to social interactions by inhibiting their egocentric perspective. Linguistic scaffolding from elder siblings and parents thus strengthens a child’s capacity to apprehend the abstract mind. From this, we can see that language ability and verbal interaction are essential to developing mind understanding, such as the ability to relate the actions of others to their mental states. This may contribute to the fact that existing ToM training is heavily language-based [42–44]. These language-based ToM training were explicitly designed to teach children mentalistic language and knowledge of inner states through role-playing and story-telling.

Hofmann et al. [43] conducted a meta-analysis of 45 language-based training studies that aim to improve children’s ToM performance. The meta-analysis showed that the aggregate effect size based on the comparisons of the 45 studies was moderately strong compared with the control group. Numerous studies in the meta-analysis appeared to have a significant impact on children’s ToM development, including having an explicit conversation about the mental states of others and emotion understanding [45, 46]. The research showed that explicit instruction could be used to teach and enhance one’s theory of mind [43]. Hofmann and colleagues emphasized the role of language in children’s ToM development, specifically, the importance of language in drawing children’s attention to mental states understanding. Consistent evidence has suggested that children’s language ability is associated with their ToM ability [5, 12, 26, 47]. However, the mechanisms underlying this relationship are still under debate. In the light of this, this paper proposes a novel view using the perspective of embodied cognition to address the competing theoretical accounts of ToM development.

### Embodied cognition

Embodied cognition is the idea that abstract mental representations are grounded in concrete sensorimotor experiences drawn from our bodily states, motions, and interactions with the surrounding environment [48–50]. Or, to put it another way, individuals perceive the world through their sensorimotor experience [51]. Previous studies have shown that individuals' current bodily experiences can influence higher cognition, such as thinking, reasoning, and evaluation during decision-making [52–54]. Empirical evidence supports this notion of the workings of the mind: In Williams and Bargh’s [55] research, participants experienced increased physical warmth or cold by holding a warm or cold object. It was the found that participants who had felt physical warmth were more likely to judge a target individual to have a warm personality and choose a gift for a friend rather than for themselves, than participants who had held the cold objects. Another study by Chu and Kita [56] illustrated that gesturing assists spatial problem-solving. In a series of experiments, Topolinski and colleagues have demonstrated that sensorimotor experiences may contribute to one's complex cognitive process, such as memory, preference, and attitude e.g. [57–59]. These findings suggest that humans often use their bodies as a reference frame to process the perceived environmental stimuli.

The literature on embodiment offers new insights into what may promote ToM development. Embodied cognition assumes that individuals tend to think through their actual or representational sensorimotor experiences. As such, individuals' representations of the minds of others may be facilitated by adopting others' frames of reference, and imagining how the world looks to them. This cognitive process of representing others' visual experiences has been understood as visuospatial perspective-taking [60, 61]. In a recent study, Erle and Topolinski [62] investigated the connection between embodied cognition (i.e., thinking through sensorimotor experience) and embodied simulation (i.e., project mental processes based on sensation). The study found that mental alignment that induced visuospatial perspective-taking necessitated some embodied transformation. This connection occurred more often when there was an orientation disparity between the individual and the target agent.

### The role of visuospatial perspective-taking in mental state understanding

The acquisition of perspective-taking and the ability to understand others’ mental states constitutes a milestone in social-cognitive development in children [43, 63–65]. Researchers have distinguished two levels of perspective-taking [60, 61, 66]: Level-1 perspective-taking involves determining the visibility of an object for another person from different vantage points; Level-2 perspective-taking entails representing how the object looks from another person's viewpoint.

Visuospatial perspective-taking is similar to level-2 perspective-taking as it involves visualizing how the world appears to another person [62]. Individuals engage in this when their frame of reference differs from that of another [67, 68]. Research reveals that visuospatial perspective-taking becomes more difficult as the angular disparity between the viewpoint of an individual and that of others increases. In a visuospatial perspective-taking paradigm, participants were shown an avatar sitting at a table with two objects. They were instructed to determine whether the avatar should use the right or left hand to pick up one of the two target objects. The experiments revealed that the reaction time of visuospatial perspective-taking increases with larger angular disparity between the participant and the avatar [60, 69].

Building on the notion of embodied cognition, this study proposes that the representation of the mind and emotion of others, i.e., psychological perspective-taking, is grounded in the representation of others’ visuospatial frame, i.e. it is grounded in visuospatial perspective-taking. Indeed, a growing body of evidence supports the close linkage between visuospatial and psychological perspective-taking [70]. For instance, children with autism spectrum disorder exhibit deficits in both visuospatial perspective-taking and empathy (which involves psychological perspective-taking) [71, 72]. Previous research has also found that visuospatial perspective-taking correlates with the personal disposition of empathy and social skills [73–77]. Schurz et al. [78] conducted a meta-analysis of fMRI studies, revealing that overlapping brain regions were involved in visuospatial perspective-taking and theory of mind. In a series of experiments, Erle and Topolinski [62] illustrated that adult participants were more likely to adopt the random thoughts of the target after they were prompted to take the target's visuospatial perspective. Moreover, the results showed that imagining the target's visual frame also increased the perceived similarity and liking for the target. In a recent study, Tian et al. [79] demonstrated a relation between spatial ability and theory of mind in 3.5- to 4-year-olds, and importantly, such relation is mediated by the young children’s visuospatial perspective-taking ability. The authors argued that the psychological mechanism of taking others’ visuospatial perspective may be involved in theory-of-mind development.

If we take the above studies together, we can see that there is strong empirical evidence to argue that simulating the visual world of another person may foster the representation of other's mind and emotional states. As such, scholars have begun to debate the sequence of the development of visuospatial and psychological perspective-taking. And whilst Moll and Kadipasaoglu [80] have argued that understanding the simple mental states of others emerges earlier than visuospatial perspective-taking, there is generally more evidence that suggests otherwise. More scholars regard visuospatial perspective-taking as an essential stepping-stone for the fully developed theory of mind [71, 81, 82].

### The present study

This proposal draws on the literature of embodied cognition and visuospatial perspective-taking to explore alternative approaches to promote early mind and emotion understanding. The potential role of visuospatial perspective-taking in developing ToM and emotion understanding prompted us to design a visuospatial-based ToM training. The study aims to determine whether training young children’s visuospatial perspective-taking promotes their theory of mind and emotion understanding.

This study involves two training studies to investigate the causal relationship between visuospatial perspective-taking and mental state understanding. In study 1, children aged 4.5 years will be randomly assigned to participate in either (a) altercentric block building (experimental group) or (b) egocentric block building (control group). Experimenters will train children’s visuospatial perspective-taking through a series of block-building activities. Several studies have shown that block building fosters young children’s spatial development [83–85]. The training structure is to reproduce block figures because this task provides abundant age-appropriate experiences for children to grasp the visuospatial relations between objects. It should be noted that this study will specifically train young children to become visuospatial perspective-takers by requiring them to adopt the visual frame of their play partner (i.e., *altercentric block building*). In contrast, children in the control group will be required to reproduce the model figure that looks the same from their own viewpoint (i.e., *egocentric block building*). The partner’s perspectives are irrelevant; subsequently, children’s visuospatial perspective-taking will not be trained. Two research questions will be addressed in study 1: Is children’s visuospatial perspective-taking associated with their ToM and emotion understanding?Do children trained in the visuospatial perspective-taking group improve significantly more than the control children in ToM and emotion understanding after 6 weeks of training?

Previous studies have found that participating in block-building tasks enhances children’s general spatial and mathematics abilities [83, 84, 86, 87]. These two skills will be assessed as a manipulation check to ensure the training improves children’s relevant skills. In this way, any absence of effects will unlikely be attributable to manipulation failure.

The main goal of study 2 is to determine whether visuospatial perspective-taking or conventional verbal training is more effective in enhancing children’s mind and emotion understandings. ToM training has mostly been heavily language-based because the literature has identified language as a strong correlate of ToM development [42, 44]. Visible social interaction without language input does not promote false-belief understanding. Hence verbal interaction is regarded to be crucial to mind understanding [88]. Moreover, a study by Lohmann and Tomasello [44] involving 3-year-old children also found that training on the theory of mind with minimal linguistic interaction was ineffective in improving children’s false belief understanding. On the basis of the embodiment framework, study 2 will investigate whether simulating the visuospatial experiences of others alone, i.e. *without* the presence of verbal communication, is sufficient to enhance mind and emotion understanding. By doing this, study 2 will compare the training effect caused by visuospatial perspective-taking to the one caused by mere verbal interaction. In study 2, children aged 4.5 years will be randomly assigned to participate in either (a) *socialised altercentric block building* (both visuospatial perspective-taking and verbal interaction), (b) *parallel altercentric block building* (visuospatial perspective-taking only), or (c) *paired dialogic reading* (verbal interaction only). Dialogic reading will be served as a promising interactive approach because this training involves back-and-forth verbal exchanges between children. In addition, dialogic reading is easy to administer with preschool children. The differences between groups in ToM and emotion understanding post-training would indicate whether visuospatial perspective-taking or verbal interaction group will be more effective in fostering mental state understandings. Two research questions will be addressed in study 2:

(1) What is the difference between the effect of visuospatial perspective-taking vs. general verbal interaction training on improving preschoolers’ ToM and emotion understanding?

(2) Do children trained in the socialised altercentric block building group improve significantly more than children in the parallel altercentric block building and paired dialogic reading groups in ToM and emotion understanding after 6 weeks of training?

## Research plan and methodology

### Study 1: examining the role of visuospatial perspective-taking in developing theory of mind and emotion understanding

#### Participants

Participants will consist of 96 typically developing Cantonese speaking 4.5-year-olds (48 males; 48 females). The targeted age group is 4.5-year-old children because the ontogenetic development of both ToM and emotion understanding abilities typically emerges at around 4 to 5 years of age [89].

This study will investigate the effect of visuospatial perspective-taking training on children’s ToM and emotion understanding abilities by capitalizing on their mind-understanding differences at this age. Several meta-analyses have reported moderate to large effect sizes for ToM, emotion understanding, and relevant spatial training [43, 90, 91]. The effect size of this study can thus be reasonably estimated as medium-to-large. We used G*Power 3.1 to conduct an a priori power analysis to determine the required sample size. Results indicated that a total sample of 79 participants was required to achieve a power of 0.80 for detecting a medium-to-large effect (*f* = 0.32) at an alpha of 0.05 for a MANOVA (MANOVA: Repeated measures, within-between interaction). To account for a potential attrition rate of 20%, we propose to recruit 48 children per group, thus 96 children in total, via electronic fliers on local internet groups.

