#### Design and procedures

This research proposal has gained approval from the Human Research Ethics Committee of [blinded university]. Written informed consent will be obtained from all participants' parents or legal guardians before the initiation of the study. Parents or legal guardians will be asked to complete a set of questionnaires on family demographics, children's characteristics and executive functioning. Prior to the training, children will first complete a pre-test in a quiet room at the University. Then, children will be randomly assigned to either the (a) egocentric block building or (b) altercentric block building training group. The training period will be six weeks, with a 1.5-h training session per week. The training will be conducted in a child-friendly lab at the University. After the training sessions are completed, the children will be tested with the same battery of measures in the post-test. Upon completion of the training, the participants' parents or legal guardians will receive a report of their child's performance and a gift voucher valued at HKD$200.

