#### Data analysis plan

First, we will perform correlation analyses with the pre-test data to examine the associations among visuospatial perspective-taking and ToM and emotion understanding. We hypothesise that there will be positive relationships among preschoolers' visuospatial perspective-taking, ToM, and emotion understanding.

We then will use independent *t*-tests to test the group differences in nonverbal reasoning, inhibitory control, and oral language proficiency and decide if these three variables will be used as covariates in subsequent analysis. Next, we will use repeated measures ANOVAs to examine the post-training improvements in general spatial and mathematics skills in both groups. Previous research has illustrated a positive effect of block-building on preschoolers’ spatial and mathematics skills [83, 84, 86, 87]. We will also examine if the altercentric block-building group improves significantly more than the egocentric block-building group in visuospatial perspective-taking. This will ensure that the altercentric training increases visuospatial perspective-taking that we aim to train.

In the main analysis, we will use repeated measures MANOVAs to determine the post-training changes in understanding mind and emotion across the two groups. We predict that the altercentric block-building group will show greater improvements in ToM and emotion understanding abilities than the egocentric block-building group. Moreover, these improvements will be mediated by the improved visuospatial perspective-taking ability.

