### Study 2: Comparing the roles of visuospatial perspective-taking and verbal interaction in developing theory of mind and emotion understanding

#### Participants

This study will compare the effects of three different training methods on the development of mind and emotion understanding in preschool children. Participants will consist of 120 typically developing Cantonese-speaking 4.5-year-olds (60 males; 60 females), with 40 children in each training group. We used G*Power 3.1 to conduct an a priori power analysis to determine the required sample size. Results indicated that a total sample of 98 participants was required to achieve a power of 0.80 for detecting a medium-to-large effect (*f* = 0.32) at an alpha of 0.05 for a MANOVA (MANOVA: Repeated measures, within-between interaction). To account for a potential attrition rate of 20%, we propose to recruit 40 children per group, thus 120 children in total, via electronic fliers on local internet groups.

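### Recruiting 96 and 120 children does not leave the required 79 and 98 after the stated 20% attrition; power for the sized test is about 0.79, and the single-outcome basis of that power should be stated

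*Protocol article*

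**What the plan says.** In the protocol article, the Participants section of Study 1 reports that "a total sample of 79 participants was required to achieve a power of 0.80", with inputs given as "power of 0.80 for detecting a medium-to-large effect (*f* = 0.32) at an alpha of 0.05". The procedure named is "MANOVA (MANOVA: Repeated measures, within-between interaction". The section then sets recruitment: "To account for a potential attrition rate of 20%, we propose to recruit 48 children per group, thus 96 children in total".

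The Participants section of Study 2 uses the same effect size, alpha and procedure for three groups. It reports that "a total sample of 98 participants was required to achieve a power of 0.80" and continues: "To account for a potential attrition rate of 20%, we propose to recruit 40 children per group, thus 120 children in total".

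Neither section names the outcome, the number of outcomes or the number of measurements behind the calculation. Under Design and procedures for Study 1 there are two occasions, a pre-test and a post-test: "the children will be tested with the same battery of measures in the post-test". The Study 1 Data analysis plan states: "we will use repeated measures MANOVAs to determine the post-training changes in understanding mind and emotion across the two groups". The Study 2 Data analysis plan names three outcomes for its MANOVAs: visuospatial perspective-taking, theory of mind and emotion understanding.

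**The concern.** An attrition allowance should leave the required number of children once the assumed loss has occurred. In both studies it leaves two or three too few. The totals look as if the required number was multiplied by 1.2 rather than divided by 0.8.

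It is also unclear what the 0.80 refers to. The main analysis of Study 1 covers two outcomes, but the required number is the one for a single outcome. If Study 1 ends without a significant group difference, readers will use the power statement to judge whether the study was large enough. They would need to know how many children the figure assumes and which test it describes.

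**Working it through.** **Inputs from the article.** f = 0.32, alpha = 0.05, target power 0.80. Study 1: 2 groups, 79 required, 96 recruited. Study 2: 3 groups, 98 required, 120 recruited. Attrition is 20% and there are two occasions.

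**1. Reproducing the required numbers.** With two occasions and one outcome, the group-by-time test is an F test on change scores with df1 = k − 1, df2 = N − k and noncentrality λ = N × f², where k is the number of groups and f² = 0.1024.

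| Study | N | df1, df2 | λ | Power |
|---|---|---|---|---|
| 1 | 78 | 1, 76 | 7.987 | 0.797 |
| 1 | 79 | 1, 77 | 8.090 | 0.802 |
| 2 | 97 | 2, 94 | 9.933 | 0.799 |
| 2 | 98 | 2, 95 | 10.035 | 0.804 |

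So 79 and 98 are the smallest totals that reach 0.80 for one outcome. The alternatives tried do not give them (Study 1 and Study 2 respectively):
- two outcomes tested jointly in G*Power's form: 98 and 61
- three change scores, which is also the case of four measurements: 111 and 70
- univariate repeated measures ANOVA with correlation 0.5: 22 and 27

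**2. Attrition.**
- Study 1: 96 × 0.8 = 76.8, below 79. Needed: 79/0.8 = 98.75, so 99, or 100 for equal groups. Tolerated loss: 1 − 79/96 = 17.7%.
- Study 2: 120 × 0.8 = 96, below 98. Needed: 98/0.8 = 122.5, so 123, which divides equally by three. Tolerated loss: 1 − 98/120 = 18.3%.
- Multiplying instead gives 79 × 1.2 = 94.8 and 98 × 1.2 = 117.6. Rounded up to equal groups, these are consistent with 96 and 120.

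**3. Power of the sized test after 20% loss.**

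| Study | Completers | λ | Power |
|---|---|---|---|
| 1 | 76 | 7.782 | 0.786 |
| 1 | 77 | 7.885 | 0.792 |
| 2 | 96 | 9.830 | 0.795 |

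**4. Study 1 if the main MANOVA is a joint two-outcome test.** At N = 76, df1 = 2 and df2 = 73. Let r be the correlation between the two change scores. The article gives no value for r, so a range is shown.

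| Assumption | λ | Power at N = 76 |
|---|---|---|
| Multivariate f = 0.32 | 76 × 0.1024 = 7.782 | 0.69 |
| Both outcomes f = 0.32, r = 0.5 | 7.782 × 2/(1 + 0.5) = 10.377 | 0.81 |
| Both outcomes f = 0.32, r = 0 | 7.782 × 2/(1 + 0) = 15.565 | 0.94 |
| Only one outcome f = 0.32, r = 0 | 7.782/(1 − 0²) = 7.782 | 0.69 |
| Only one outcome f = 0.32, r = 0.3 | 7.782/(1 − 0.3²) = 8.552 | 0.73 |
| Only one outcome f = 0.32, r = 0.5 | 7.782/(1 − 0.5²) = 10.377 | 0.81 |

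**5. Study 2 as a joint test at N = 96.** If f = 0.32 is one total effect, power is 0.695 with two outcomes and 0.62 with three. Under G*Power's own multivariate effect-size convention it is 0.956 and 0.927. The article does not say which definition applies.

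**The case against.** The proven shortfall is two or three children per study and costs at most about 1.6 power points (0.802 to 0.786). The 20% is itself only a possible loss, and no design decision turns on the difference. That stands, and it sets the severity. It does not make the sentence correct, because the allowance is said to cover a loss that it does not cover.

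A reader might go further and infer that the power calculation belongs to a different test from the planned one, and that the plan is therefore substantially underpowered. The documents do not support this, for four reasons:
- The single-outcome basis is inferred from exact reproduction. The inference is strong, but the article does not state it.
- The analysis plans speak of MANOVAs in the plural, which can mean one repeated measures test per outcome. The calculation then fits the plan, and each test keeps about 0.79.
- If Study 1 does use a joint test, its power at 76 completers runs from 0.69 to 0.94, depending on how f is defined and on the correlation of changes. The lower figure is only one of these cases.
- In Study 2 even the direction of the change depends on the definition of f.

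Nor does the article plan to split alpha between outcomes, so power at a reduced alpha is not a test of what it says.

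**Conclusion.** The attrition statement is wrong as written in both studies. On the article's own figures 76 to 77 and 96 children remain against 79 and 98 required. Power for the sized test is 0.786 to 0.792 and 0.795 rather than 0.80, and the tolerated loss is about 18%. The head counts and tolerated losses follow from the stated numbers alone. The power figures assume one outcome at two occasions, an assumption supported by the exact match to both required totals.

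The second part is a request for clarity: the article should say that 0.80 is the power for a single outcome. Whether a joint test in Study 1 has less or more than that cannot be settled from the article, and no joint-test power loss is established for Study 2. Overall severity is minor.

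**What to change.** Keep 96 and 120. In each Participants section, make one of two corrections:
- state that after 20% attrition 76 to 77 (Study 1) and 96 (Study 2) children remain, giving power of about 0.79 in each study at f = 0.32; or
- state that the totals preserve 79 and 98 completers with attrition up to about 18% (17.7% and 18.3%).

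Add a sentence saying that the calculation is for a single outcome measured at pre-test and post-test. If the main MANOVA of Study 1 tests theory of mind and emotion understanding jointly, report the power of that test separately, giving the assumed effect on each outcome and the assumed correlation between changes.

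The cost is a few restated figures and one added sentence per study, plus a short joint-test calculation for Study 1 if it applies. No extra children are needed.
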